## Abstract

**Objective:** In an effort to make tuberculosis (TB) guidelines issued by the World Health Organization (WHO) more accessible for stakeholders, we developed a new electronic map of tuberculosis recommendations (eTB RecMap). The objective of this study is to compare the accessibility of the new eTB RecMap to the conventional method of accessing TB recommendations using the WHO website.

**Study Design:** We will conduct a two-arm superiority randomised controlled trial among stakeholders who were past or planned future users of TB guidelines. Using a 1:1 ratio, we will randomly assign participants to complete an activity using the WHO eTB RecMap or the conventional website. We will compare the outcomes of accessibility, understanding, satisfaction and preference between groups.

### Keywords

Guideline; Recommendation; Tuberculosis; GRADE; Evidence-Based Practice; Evidence to Decision Table

### Trial Registration

This trial is registered with ClinicalTrials.gov (NCT04745897).

### Funding

The development of the eTB RecMap was funded by the WHO. This trial was not funded by the WHO, and the WHO will not be involved in data collection or analysis of study findings.

### Consent to Participate

The study questionnaire includes a consent statement that described the study purpose, confidentiality, risks, and voluntary participation.

### Data Protection and Confidentiality

Anonymized survey data will be stored in SurveyMonkey® password-protected software. Participant names collected for follow-up will be stored in a separate document on a secure password-protected computer. Only the research team will have access to these data.

### Ethics Approval

Hamilton Integrated Research Ethics Board (HiREB)

## Abbreviations

**EtD:** Evidence to Decision

**GDG:** Guideline Development Group

**G-I-N:** Guidelines International Network

**GRADE:** Grading of Recommendations Assessment, Development and Evaluation

**HIC:** high-income country

**LMIC:** low- and middle-income country

**NICE:** National Institute for Health and Care Excellence

**RCT:** Randomised Controlled Trial

**eTB RecMap:** Electronic Map of Tuberculosis Recommendations

**SoF:** Summary of Findings

**TB:** Tuberculosis

**UN:** United Nations

**WHO:** World Health Organization

**WHO GTB:** WHO Global TB Programme

## Background

Tuberculosis (TB) is the leading cause of death from a single infectious agent worldwide, with an estimated 10 million new cases in 2019. In a concerted effort to end the TB epidemic, the WHO Global TB Programme (WHO-GTB) has issued guidelines with recommendations on TB prevention, diagnosis, treatment, and care. Since 2009, these guidelines have been developed using the Grading of Recommendations Assessment, Development and Evaluation (GRADE) method, which is a transparent, evidence-based framework for the assessment of the certainty in a body of evidence and recommendation development. Specifically, GRADE assists guideline developers in question prioritization, certainty assessments, balancing benefits and risks, and considering, among other criteria, cost, equity, acceptability, and feasibility in context.

WHO TB recommendations are located in many discrete publications on the WHO website, including standard, consolidated, interim, and emergency guidelines. Given the large number and variety of publications, ways to enhance their connectivity and accessibility should be explored like for guidelines in other fields. A mixed-methods study by Hajizadeh, et al. suggested that stakeholders, including members of the WHO-GTB guideline development group (GDG), desire direct access to WHO TB recommendations and supplementary information, such as evidence to decision (EtD) tables and evidence profiles.

In an effort to improve accessibility and use of WHO TB recommendations, we developed a WHO eTB recommendation map (RecMap) in a collaboration between the WHO Collaborating Center for Infectious Diseases, Research Methods and Recommendations, the Michael G DeGroote Cochrane Canada Centre and the WHO-GTB. This RecMap identifies, lists, and maps WHO TB recommendations using recommendation mapping methodology. This methodology visually organizes recommendations, thus allowing the identification of clusters and gaps. Furthermore, it is anticipated to facilitate the adoption, adaptation, or de novo development of recommendations in a variety of countries and settings through an integrated linkage and access to original content on GRADEpro.

In order to compare the accessibility of the new WHO eTB RecMap with the conventional method of accessing TB recommendations using the WHO website, we will conduct a randomised controlled trial.

## Methods

This study will be reported in accordance with the most recent guidance from the Consolidated Standards of Reporting Trials (CONSORT). We registered the trial with ClinicalTrials.gov (trial registration: NCT04745897).

### Study Setting

This study was a two-arm randomised controlled superiority trial to compare the accessibility of the WHO eTB RecMap (WHO eTB) to the conventional method of accessing TB recommendations through the WHO publications website (WHO TB). It will be administered

using a SurveyMonkey® questionnaire, accessible through a link shared via email. Participants will respond to demographic questions and will subsequently be randomised using 1:1 allocation to access a recommendation using either WHO eTB or WHO TB (platforms). Randomization is stratified by participant background (e.g. patient, healthcare provider, policymaker) in order to ensure balance between groups. Participants will complete Likert-scale and multiple-choice questions about the platform which they were allocated. After completing the key portion of the trial, they will receive information about the alternative platform to respond to a question on their preference.

**Figure 1.** Survey RCT Flow Diagram

[figure not shown]

## Participants

### Eligibility Criteria

Stakeholders who consider themselves to be users or potential users of TB guidelines, recommendations, and policy advice are eligible. For the purposes of this trial, we define a user as someone who responds “yes” to the question “have you ever accessed TB guidelines, recommendations or policy advice in the past?”. A potential user is someone who responds “yes” to the question “do you plan on accessing TB guidelines, recommendations or policy advice in the future?”. Eligible participants could be part of any group with a stake in TB, including the public, healthcare providers, policymakers, and researchers, and there are no restrictions on

country of origin, level of education, or prior TB work experience. Individuals who were involved in WHO eTB development are not eligible, thus will not be invited to participate.

Recruitment

We will use a targeted snowball recruitment strategy by emailing survey links to WHO TB Guideline Development Group (GDG) members, program managers, and other stakeholders involved in the process of using and applying TB guideline recommendations. We will request that these members disseminate the survey within their networks, which may have included healthcare providers, policymakers, researchers, and people living with TB. Furthermore, we plan to share the survey link with TB, infectious disease, and guideline groups on the social media platforms Twitter and LinkedIn.

Intervention and Comparison

In this randomised controlled superiority trial, the intervention is the new WHO eTB RecMap (WHO eTB), and the comparison is the conventional method of accessing TB recommendations using the WHO website (WHO TB). We will ask survey participants to complete an activity in searching for the same recommendation using the one platform which they had been randomly allocated. Instructions and questions for both arms are worded as similarly as possible. See Table 1 for an overview of the differences between WHO eTB and WHO TB.

| Table 1. Description of differences between WHO TB and WHO eTB |            |                           |                            |
|----------------------------------------------------------------|------------|---------------------------|----------------------------|
|                                                                |            | WHO TB                    | WHO eTB                    |
| Website                                                        | Search     | WHO website               | WHO eTB website            |
|                                                                |            | PDF documents             | Search bar and filters     |
| Strength and certainty defining the recommendation             |            | Often near recommendation | Always near recommendation |
|                                                                | EtD tables | Separate appendix         | Link to page in appendix   |
| Recommendation mapping                                         |            | No                        | Yes                        |

Abbreviations: WHO TB, accessing World Health Organization tuberculosis recommendations via the World Health Organization’s website; eTB, the new eTB recommendations map; PDF, portable document format; EtD, evidence to decision tables

Outcomes

This trial uses several of the outcomes that have been validated in the evaluation of GRADE Summary of Findings (SoF) tables and are defined as follows.

Primary Outcome

Accessibility of Information

The primary outcome of interest is the accessibility of information available on the WHO eTB compared to WHO TB. We define accessibility as the ability to access and use the presented information. This outcome considers the four following domains: (1) how easy it was to find the

information (2) how easy it was to understand the information (3) whether the presentation facilitated decision-making (4) whether the website was easy to navigate. We will use the composite of these four outcomes as primary outcome (see statistical analysis), and the individual domains will also be analyzed as secondary outcomes.

## Secondary Outcomes

### *Understanding*

We define understanding as the correct comprehension of findings. This outcome will be measured using three multiple-choice questions with five choices and one correct answer. The questions are: ‘what is the recommendation strength?’, ‘what is the certainty of the evidence?’ and ‘on which page does the EtD table for this recommendation start?’.

### *Satisfaction*

We define satisfaction as a stakeholder’s impression of platform presentation. This outcome considers the presentation of three domains: (1) home page (2) recommendation list (3) individual recommendation.

### *Preference*

We define preference as a greater liking of one platform over the other. All participants will be provided with a short demonstration of both platforms. They will subsequently be asked ‘between the WHO Tuberculosis Guidelines (current website), and the WHO eTB Guidelines (alternative website), which do you prefer?’.

## Outcomes Measurement

We will use the original Likert-scale to obtain responses for the outcomes of accessibility and satisfaction. We will measure preference using a Likert-type scale to express the degree of preference with seven answer options (1 = strongly prefer WHO TB, 2 = prefer WHO TB, 3 = somewhat prefer WHO TB, 4 = same preference for WHO TB and eTB, 5 = somewhat prefer WHO eTB, 6 = prefer WHO eTB, 7 = strongly prefer WHO eTB).

## Sample Size Calculation

Sample size was calculated using the primary outcome of accessibility in WINPEPI® (PEPI-for-Windows) version 11.65. For this two-sided ( $\alpha = 0.05$ ) superiority analysis, these computations were made based on a t-test with the null hypothesis that there is no difference between the WHO eTB and WHO TB in the accessibility of information.

$H_0$ : WHO eTB = WHO TB

$H_1$ : WHO eTB  $\neq$  WHO TB

With sample sizes of 122 per arm (244 total) we would achieve 80% power to detect a difference on the Likert-scale of 0.5 (effect size) with a standard deviation of 1.0 between intervention and control groups. We applied the effect size and standard deviation from previous studies on GRADE SoF tables. We assumed that 15% of those starting would not complete the survey, but we did not factor stratifying participants by stakeholder group into the calculation, as the aim of stratification was to balance participants rather than be sufficiently powered to detect subgroup effects.

### Randomization

Participant response to a question on their role as a participant in this study will be used for stratification into one of four categories described in Figure 1. Participants within each of these categories will be randomly assigned in a 1:1 ratio to the WHO eTB or WHO TB arms.

Participants will also be randomly assigned to access one of two recommendations in a 1:1 ratio. The same two recommendations will be presented for both arms and selected because they contain mostly plain language and were more accessible to non-clinical participants.

### Allocation Concealment

The allocation sequence is concealed using SurveyMonkey® software based on a commercial, but unknown algorithm without a pre-identified sequence.

### Blinding

Participants will not be aware of their random allocation to WHO eTB or WHO TB until disclosure (see Figure 1). Thus, participants will be blinded for all outcomes except the secondary outcome of preference. Neutral language is used in both trial arms to prevent promotion of the intervention or comparison. Nevertheless, some participants may have accessed WHO TB recommendations in the past and a small number may have been aware of the development of WHO eTB.

### Consultation and Pilot Testing

We will perform a pilot test for survey length, question relevance, and question clarity. Participants will be researchers and information technology developers affiliated with McMaster University. Revisions will be made to the questionnaire using pilot test feedback. Pilot test participants will not be included in the final analysis.

### Statistical Analysis

We will conduct the analyses using IBM SPSS® (Statistical Package for Social Sciences) version 23.

### Descriptive Analysis

We will summarize participant baseline characteristics and outcomes using means and standard deviations (SD) for continuous variables, and proportions for categorical variables.

### Inferential Analysis

We will perform a primary analysis including all randomised participants, except for those who completed the survey in less than five minutes. We determined this cut-off a priori because user testing determined that it would be impossible to complete the work in that time. We will conduct a second per-protocol analysis which excludes participants who were flagged by SurveyMonkey® software (see below). For the outcomes of accessibility and satisfaction, we will use t-tests and mean differences 95% confidence intervals (95% CIs) to compare means and standard deviations (SDs) between the intervention and control groups. For the outcome of understanding, we will use  $\chi^2$  tests and risk difference (RD) with 95% CIs to compare the proportion of correct responses between groups. Finally, for preference, we will present preference as mean (SD) overall and for both trial arms. Skewness, Shapiro-Wilk tests, and histograms will be used to evaluate whether the distribution was shifted toward the same preference in both groups. Levene's test of equal variances will be used for all t-tests and degrees of freedom were adjusted for  $p < 0.05$ . We will report all p-values to three decimal places, with values less than 0.001 reported as  $< 0.001$ .

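### The planned tests use neither the stratification factor nor the randomised recommendation: they stay valid or conservative, but give up precision that data already collected would supply

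*Protocol*

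**What the plan says.** Two features of the design bear on the analysis.

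- **Stratification.** Protocol, Study Setting: "Randomization is stratified by participant background (e.g. patient, healthcare provider, policymaker) in order to ensure balance between groups". Protocol, Randomization: the participant's stated role "will be used for stratification into one of four categories described in Figure 1", and "Participants within each of these categories will be randomly assigned in a 1:1 ratio to the WHO eTB or WHO TB arms".
- **A second randomised factor.** Protocol, Randomization: "Participants will also be randomly assigned to access one of two recommendations in a 1:1 ratio". No balancing of recommendation against arm or stratum is described.

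The mechanism is left open. Protocol, Allocation Concealment, says that assignment is "based on a commercial, but unknown algorithm without a pre-identified sequence". No blocks are mentioned.

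Protocol, Inferential Analysis, then names the tests. For the primary outcome: "For the outcomes of accessibility and satisfaction, we will use t-tests and mean differences 95% confidence intervals (95% CIs". For understanding: χ² "tests and risk difference (RD) with 95% CIs to compare the proportion of correct responses between groups". Neither stratum nor recommendation enters any of these analyses. The Sample Size Calculation section explains why strata were left out of the sample size (they serve balance, not subgroup power). It gives no reason for leaving them out of the analysis.

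**The concern.** When randomisation is forced to balance on a factor that predicts the outcome, the variance of the difference in means falls, but the ordinary two-sample standard error does not reflect the fall. The analysis then understates its own precision. When balance is not forced, the factor still explains variance that an adjusted analysis would remove. Either way, prognostic information that the trial already holds goes unused.

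At stake are the width of the interval for the accessibility composite and, to a lesser degree, power. The choice also leaves the stated purpose of stratification half served. If the algorithm does not in fact balance within strata, only the analysis can take account of stakeholder type. Exclusion of participants who finish in under five minutes, and available-case analysis, could also disturb balance in the analysed set even if assignment was blocked.

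**Working it through.** **Inputs from the Protocol (Sample Size Calculation).** Difference δ = 0.5, SD σ = 1.0, two-sided α = 0.05, 122 per arm (244 total), stated power 80%, 15% non-completion. The basis is a t-test: "these computations were made based on a t-test with the null hypothesis that there is no difference between the WHO eTB and WHO TB".

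**Assumed input.** The share of outcome variance explained by the factors (R²) is not in the Protocol. It is varied from 0 to 20%.

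**1. The plan's own figure.** n per arm = 2(1.96 + 0.842)²σ²/δ² = 2 × 7.85/0.25 = 62.8, so 63 (64 with the t distribution), or 75 to 76 after 15% non-completion. The stated 122 does not follow from the stated inputs. At 122 per arm, SE = √(2/122) = 0.128 and power = Φ(0.5/0.128 − 1.96) = 97.4%. That discrepancy is a separate matter. It is used here only to set the baseline power.

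**2. Size of the unadjusted test if balance within strata is enforced.** The true SE is √(1−R²) times the one used, where R² is the share due to stratum alone. The SE used is therefore too large by a factor of 1/√(1−R²), and the true size is 2[1 − Φ(1.96/√(1−R²))].

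| Stratum R² (assumed) | SE too large by | True size |
|---|---|---|
| 5% | 2.6% | 4.4% |
| 10% | 5.4% | 3.9% |
| 20% | 11.8% | 2.8% |

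**3. Precision and power with adjustment.** The half-width is 1.96√(1−R²)√(2/122), where R² is now the total for stratum and recommendation. Power is Φ(0.5/(0.128√(1−R²)) − 1.96).

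| Total R² (assumed) | 95% CI half-width | Narrower by | Power, 122 per arm | Power, 104 completers per arm |
|---|---|---|---|---|
| 0 | 0.251 | – | 97.4% | 95.0% |
| 5% | 0.245 | 2.5% | 98.0% | 95.9% |
| 10% | 0.238 | 5.1% | 98.5% | 96.7% |
| 20% | 0.224 | 10.6% | 99.2% | 98.1% |

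The last column takes 122 as the number starting: 122 × 0.85 = 103.7.

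**4. Simulation check.** 244 participants, four strata with assumed shares of 10%, 50%, 15% and 25%, no true effect, 20,000 trials per setting (Monte Carlo standard error about √(0.05 × 0.95/20,000) = 0.0015).

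- *Blocks of four within strata, stratum R² 10% and 20%:* the t-test rejected in 3.8% and 2.8% of trials, matching step 2. The adjusted model rejected in 4.8% to 5.1% across all blocked settings that were run.
- *Simple assignment:* the t-test rejected in 4.8% to 5.1% when only stratum was prognostic, and in 4.8% to 5.4% over all settings.
- *Recommendation prognostic alone (R² 10%), assigned independently:* the t-test rejected in 4.8% to 5.0% under either scheme.
- *Blocks, stratum R² 10% plus recommendation R² 10%:* the t-test rejected in 3.7%. This is close to the 3.9% for stratum alone and not to the 2.8% that a pooled 20% would give. Recommendation therefore does not lower the size.
- *CI width under blocks:* 0.504 to 0.479 at R² 10% (5.0% narrower) and 0.504 to 0.452 at R² 20% (10.4% narrower). At R² = 0, adjustment widened the interval by less than 1% (0.505 to 0.509 under simple assignment).

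**The case against.** The strongest reply is that the plan is coherent on its own terms. The sample size rests on a t-test, the analysis is a t-test, and stratification is declared to be for balance. Power is high on the stated inputs. The Protocol gives no evidence that either factor is prognostic. It says that both recommendations were chosen for plain language and accessibility to non-clinical participants, which may make the two behave alike. The stratum labels are in a figure that is not shown. All of this stands, and it limits the point to a gain whose size rests on an assumed R².

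Three stronger readings are tempting, and the documents do not support them.

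- *A reader might infer that the confidence intervals and p-values do not fit the design.* That is true only for the stratification factor, only if balance within strata is enforced (which the Protocol does not establish), and then only in the conservative direction. Nothing here raises the false-positive risk.
- *A reader might apply the reduced test sizes to stratum and recommendation together.* The Protocol describes a separate 1:1 assignment to recommendation, and under independent assignment the t-test keeps its level. Only the stratum share of R² matters for size.
- *A reader might infer that a chance imbalance biases the comparison.* Under simple assignment a stratum of 30 (an assumed size, since the Protocol gives none) has about a 10% chance of a split of 2:1 or worse. The unadjusted standard error already covers that variability, so the cost is precision and not validity.

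That an unseen statistical analysis plan may exist is only a partial answer, because the Protocol already names unadjusted tests.

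**Conclusion.** The point holds as a free improvement. It does not show the planned analysis to be invalid. The Protocol fixes unadjusted tests although it stratifies by four stakeholder categories and randomises the recommendation.

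With enforced balance and a prognostic stratum, the t-test is conservative, with the sizes in step 2. With simple assignment, and for the recommendation in either case, it is valid but less precise. At a total R² of 10% to 20% the interval is about 5% to 11% wider than it need be, counting from the unadjusted width. The power gain is 1 to 2 points at 122 per arm (about 2 to 3 points at 104 completers per arm).

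These sizes rest on the assumed R², on the stated difference and SD, and on recommendation being assigned independently of arm. At R² = 0 the benefit vanishes and the cost is negligible.

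**What to change.** In Protocol, Inferential Analysis:

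- **Primary outcome.** Analyse the accessibility composite with a linear model on arm, stakeholder stratum (four levels) and recommendation (two levels). Report the adjusted mean difference with its 95% CI.
- **Satisfaction.** Use the same model.
- **Understanding.** Report a risk difference stratified by the same factors (for example Mantel-Haenszel), or one standardised from a logistic model on arm, stratum and recommendation.
- **Supportive analyses.** Keep the plain t-test and χ² test.

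This is sound whichever way the survey software assigns participants, so the unknown algorithm need not be resolved first. The cost is analysis wording only. Stratum is recorded before randomisation, recommendation is assigned within the survey, and the sample size need not change on this account. The documents do not show whether the named SPSS version offers each risk-difference method directly, but a Mantel-Haenszel risk difference can be computed from the stratum tables. The change should be fixed before the planned interim analysis, so that the covariates cannot appear to have been chosen after seeing data.

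### The skewness and Shapiro-Wilk tests named to assess a shift in preference measure shape, not location, and cannot support an inference about a shift

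*Protocol*

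**What the plan says.** Under Secondary Outcomes, the Protocol states: "We define preference as a greater liking of one platform over the other". Outcomes Measurement gives a seven-option scale whose midpoint is "4 = same preference for WHO TB and eTB". Lower scores favour the conventional website (WHO TB) and higher scores favour the new map (WHO eTB).

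Inferential Analysis then gives preference two sentences. The first is descriptive: "Finally, for preference, we will present preference as mean (SD) overall and for both trial arms". The second names methods and a purpose: "Skewness, Shapiro-Wilk tests, and histograms will be used to evaluate whether the distribution was shifted toward the same preference in both groups".

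The other outcomes in that paragraph are treated differently. The Protocol says "For the outcomes of accessibility and satisfaction, we will use t-tests and mean differences 95% confidence intervals (95% CIs"), and for understanding it plans chi-squared tests and risk differences with 95% CIs. For preference it names neither a confidence interval nor a test of the mean.

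**The concern.** Preference, as defined and scored, is a question about where responses lie relative to 4. The second sentence asks whether responses have shifted, which is also a question of location, but two of its three tools are measures of shape. Shapiro-Wilk asks whether a sample could come from a normal distribution. Skewness asks whether a sample is asymmetric about its own mean.

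The wording of the purpose can be read in three ways: a shift away from 4, a shift toward 4 (echoing the midpoint's label), or both arms leaning the same way. The mismatch remains under each. The first two need a comparison with 4, which neither statistic makes. The third needs the arms compared for direction, and each statistic is computed within one sample.

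The same paragraph promises that all p-values will be reported. A Shapiro-Wilk p-value below 0.001 is close to certain on seven-category data, and it would then stand next to a statement about shifted preference that it does not bear on.

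**Working it through.** **Inputs.** From the Protocol: the 1 to 7 scale with neutral at 4 (Outcomes Measurement); 122 per arm, 244 in total, and 15% non-completion (Sample Size Calculation). The sample size was set for accessibility. The Protocol states no figure for preference, so there is none to reproduce, and only the numbers of participants are used here. The response distributions and SDs below are assumptions.

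**Step 1: algebra, with no distributional assumption.** Let every score x become x + c.

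- Skewness is [Σ(x − x̄)³/n] / [Σ(x − x̄)²/n]^1.5. The mean also moves by c, so every deviation x − x̄ is unchanged, and so is the skewness.
- Shapiro-Wilk is W = [Σ aᵢx₍ᵢ₎]² / Σ(x − x̄)². The weights aᵢ sum to zero, so the numerator is unchanged. The denominator is unchanged for the reason just given.

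Numerical check on one simulated sample of 244: W = 0.908, p = 4.5 × 10⁻¹¹ and skewness −0.205. After adding 1 to every score, all three values were identical.

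**Step 2: simulation, 2,000 samples of n = 244, tests at 0.05.** The symmetric shape has probabilities 0.10, 0.20, 0.40, 0.20, 0.10 on five adjacent scores (SD 1.10).

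| Assumed distribution | Mean | Skewness | Shapiro-Wilk rejects | Skewness test rejects | t-test against 4 rejects |
|---|---|---|---|---|---|
| Symmetric, prefers WHO TB | 3.00 | 0.00 | 100% | 0.1% | 100% |
| Symmetric, neutral | 4.00 | 0.00 | 100% | 0.1% | 4.3% |
| Symmetric, prefers WHO eTB | 5.00 | 0.00 | 100% | 0.0% | 100% |
| Right-skewed, almost neutral on average | 3.98 | 0.72 | 100% | 100% | 7.0% |
| Left-skewed, strongly prefers WHO eTB | 5.63 | −1.20 | 100% | 100% | 100% |

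Shapiro-Wilk is uninformative here because it rejects in every row. The skewness test misses a full-point preference in either direction (rows 1 and 3) and rejects when there is almost no average preference (row 4). The mean separates all the cases.

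**Step 3: other sample sizes.** Normal scores rounded to 1 to 7 were simulated 1,000 times per setting at n = 104, 122, 207 and 244. With mean 4 and SD 1.0 or 1.5, Shapiro-Wilk rejected in 100% of samples, and the t-test against 4 in 3% to 6%. With mean 5 and SD 1.0, average skewness was only −0.08 to −0.10, and the t-test rejected in 100%.

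**Step 4: what a location analysis would deliver.** The 95% CI half-width for a mean is 1.96 × SD / √n, and for the between-arm difference 1.96 × SD × √(2/122). After 15% loss, 0.85 × 244 ≈ 207.

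| Assumed SD | Overall, n = 244 | Overall, n = 207 | One arm, n = 122 | Between arms, 122 each |
|---|---|---|---|---|
| 1.0 | 0.13 | 0.14 | 0.18 | 0.25 |
| 1.5 | 0.19 | 0.20 | 0.27 | 0.38 |
| 2.0 | 0.25 | 0.27 | 0.35 | 0.50 |

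For example, 1.96 × 1.0 / √244 = 1.96 / 15.62 = 0.13.

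**The case against.** A reader might infer that the plan cannot show which platform users prefer. The Protocol does not support that. The sentence just before the one at issue plans the mean (SD) overall and by arm, and the sentence at issue itself includes histograms. On a scale anchored at 4, both show direction and size. Someone who saw a significant Shapiro-Wilk result would also see whether the mean was near 4 or near 5, and with the mean, SD and number of respondents could work out an interval. This stands, and it limits the harm.

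It is also fair to say that a descriptive summary is a legitimate choice for a secondary outcome, and that a missing interval or test could be supplied in a statistical analysis plan that is not shown. Had the Protocol stopped at the mean (SD), there would be no finding. It goes further and names tests for a stated purpose that they cannot serve. That is something the document fixes badly, not a detail left for later.

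Finally, on a bounded scale a strong preference often does produce skew, as the −1.20 at mean 5.63 shows, so skewness will not always miss a preference. That stands too. But skew also appears when the mean is almost neutral (0.72 at mean 3.98) and is absent at a symmetric full-point shift, so it is not a measure of preference.

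**Conclusion.** Wrong as written, with limited consequences. That skewness and Shapiro-Wilk do not respond to location is exact and rests on no assumption. That Shapiro-Wilk rejects in practically every sample at about 200 to 244 participants rests on the simulated distributions, although it held in every setting tried. The CI widths rest on an assumed SD of 1.0 to 2.0.

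The severity is minor to moderate. Preference is a secondary outcome, it does not enter the sample size, and no decision rule depends on it. The primary accessibility comparison is untouched. What is lost is a valid inference about preference, a question that the planned sample could answer to within about 0.13 to 0.27 points overall.

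**What to change.** In Inferential Analysis, drop skewness and Shapiro-Wilk as evidence of a shift. Keep the mean (SD) overall and by arm, and keep the histograms as description. Add:

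- mean preference minus 4 with a 95% CI, overall and in each arm, with a one-sample t-test or Wilcoxon signed-rank test against 4;
- the between-arm difference in mean preference with a 95% CI, which shows whether stated preference depends on the platform a participant was assigned to use.

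Reword the purpose at the same time so that it says which question is meant: departure from neutral, agreement in direction between arms, or both.

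The cost is a change of wording and a little more analysis. No new data, questionnaire items or participants are needed.
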